#### 2.5.5. Study Groups

The control group will be told to apply their standard of care (30:2 current practice approach). Teams will have access to their usual resuscitation equipment (e.g., they will probably use an oropharyngeal cannula). The decision of whether to use any specific item will remain at the discretion of the team members, as in an actual resuscitation.

We developed an experimental approach which consists, when starting CPR in an OHCA, of delivering no prior FMV, but instead directly placing an i-gel^®^ device while the second team member performs continuous chest compression from the beginning of resuscitation manoeuvres. As soon as the device is in place, ventilations are given asynchronously at a rate of 10 per minute following AHA recommendations [1]. Paramedics and EMTs will be provided with an i-gel^®^ device size 4 (Intersurgical Ltd., Wokingham, UK) and told to apply the experimental approach. A lubricant recommended by the manikin manufacturer will be provided.

#### 2.5.6. Data Collection

Two questionnaires (Supplementary Tables S5 and S6) will be used. The demographics data questionnaire will be filled pre-scenario and will be used to gather participants’ characteristics (age, gender, years of professional experience, professional title, estimated number of i-gel^®^ insertions performed on manikin during last year, estimated number of i-gel^®^ insertion performed on real patient during the last year).

The first part of the assessment’s questionnaire will be used by the two investigators responsible for simulation during the resuscitation scenario to collect the number of attempts needed to reach successful insertion; it will be countersigned by the team leader post-scenario to limit errors (double check). All other CPR outcomes (chest compressions, shocks and ventilations) are measured by the SimMan.

The second part of the assessment’s questionnaire will be completed post-scenario by each participant to assess satisfaction using a 5-point Likert scale ranging from “Not satisfied at all” to “Very satisfied”, and cognitive load using a 9-point symmetrical category scale ranging from “Very, very low mental effort” (1) to “Very, very high mental effort” (9), as described by Paas and Van Merriënboer and previously used in simulation sessions wherein participants have to translate the perceived amount of total mental effort into a numerical value [45,46].

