### 2.9. Sample Size Calculation, Data Extraction and Statistical Analysis

The sample size is based on an estimate as there are few relevant data available to compute it for such a study. The mean time required to deliver two ventilations is estimated to be around 4 s; two ventilations should be provided 5 times during the first cycle, therefore amounting to a total of 20 s of no-flow. In addition, the initial rhythm analysis should take about 8 s. Pooled together, these no-flow times should amount to 28 s out of the first 120 s cycle, therefore representing 23% of no-flow. The CCF should therefore be around 77% in the control group. In the experimental group, taking into account the time for rhythm analysis and shock, estimated to be around 8 s (same time as control group), the corresponding no-flow time should be about 7%, with a CCF of 93%. Based on observational data from case reviews and pilot tests, the variability of the data is estimated with a standard deviation of 12.

Twenty-four teams will be required in order to have a 90% chance of detecting, at the 5% significance level, an increase in the primary outcome measure from 77 in the control group to 93 in the experimental group.

The data extraction process will take place as follows: the CPREvents.xml file will be obtained by unzipping the SSX file proposed by Laerdal after each simulation with the SimMan manikin and saved in a comma-separated values (CSV) file. Then, this file will be uploaded in an SQL table (by phpMyAdmin, https://www.phpmyadmin.net/, V. 5.0.4, accessed on 23 February 2021). The variables of interest will be automatically generated in an accurate, reliable and reproducible manner using a PHP script specifically designed for the study (Supplementary File S7), from which a new CSV file will be extracted and imported directly into the statistics software. To minimize copying or typing errors, all data collected on paper CRF will be entered in duplicate using EpiData [52]. The consistency of the answers will then be checked by merging the two files in a common variable where discrepancies are listed. After resolving the discrepancies, data will be exported in a Stata DTA file. These two Stata databases will then be concatenated. Missing data will be treated as such. No imputation technique will be used.

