All data that could allow the data analyst to identify the group allocation will be deleted (e.g., number of insertion attempts). The groups will be renamed otherwise (groups “Teysachaux” and “Moléson”) and the curated database will be sent in Stata DTA file format to DT for formal analysis. All investigators will be able to access the curated and coded data set.

Distribution normality will be checked graphically for continuous variables, and the Shapiro–Wilk test will be used in case of doubt. If this assumption is checked, a Student’s t-test will be used to compare both groups; if not, the Mann–Whitney U test will be used. These variables will be described using mean (SD) or median (Q1; Q3) depending on their distribution. We will test proportions using Fisher’s exact test. They will be reported with their 95% confidence interval.

User satisfaction will be assessed graphically, then dichotomized into “Satisfied” versus “Not satisfied” before being tested using Fisher’s exact test. The cognitive load variable will be treated as continuous.

A two-sided p-value of 0.05 will be considered significant. All the statistical analyses will be performed using Stata V15.1 (StataCorp. 2017. Stata Statistical Software: Release 15. College Station, TX: StataCorp LLC).

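### Satisfaction and cognitive load are scored by both members of each randomised team, but the named tests make no allowance for the team

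*Protocol article*

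**What the plan says.** All references are to the protocol article.

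- **Unit of randomisation.** Section 2.5.1 allocates teams, not people, to the two arms in a 1:1 ratio, stratified by service. Table 1 refers to pairs, and the Discussion says that two providers manage the scenario.
- **Unit of sample size.** Section 2.9: "Twenty-four teams will be required in order to have a 90% chance of detecting, at the 5% significance level".
- **Unit of measurement.** The manikin yields one record per team. The second part of the assessment questionnaire, however, "will be completed post-scenario by each participant to assess satisfaction using a 5-point Likert scale", and the same form carries the 9-point mental effort item (section 2.5.6).
- **Tests.** For continuous variables, section 2.9 names Student's t-test, or Mann–Whitney if normality fails, and adds that "The cognitive load variable will be treated as continuous". For satisfaction: "User satisfaction will be assessed graphically, then dichotomized into" satisfied versus not satisfied, followed by Fisher's exact test. "A two-sided p-value of 0.05 will be considered significant".

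The article does not average the two scores, select one member or model the team for these outcomes. It also does not say which of the five levels count as satisfied.

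**The concern.** Two members of a team share one allocation and one 10-minute scenario, so their ratings are not two separate pieces of evidence about the arm. All three named tests assume independent observations. Applied to individual scores, they use a standard error that ignores the pairing. It is too small if teammates tend to agree and too large if their scores move in opposite directions.

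At stake is the validity of the p-values for the two outcomes that record how providers experience the new approach. The Discussion foresees a field trial as a possible next step, and a spurious difference in mental effort or satisfaction could colour that decision.

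A smaller point concerns satisfaction. The plot comes before the split and the cut is not given, so it remains open whether the middle level counts as satisfied.

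**Working it through.** **1. The plan's own figure.** The inputs from section 2.9 are "an increase in the primary outcome measure from 77 in the control group to 93 in the experimental group" (difference 16), "the variability of the data is estimated with a standard deviation of 12", 90% power and two-sided 5%.

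n per arm = 2 x (1.960 + 1.282)² x 12² / 16² = 2 x 10.51 x 144 / 256 = 11.8, rounded up to 12.

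That is 24 teams, with power 90.4% by the normal approximation. The stated figure reproduces with the team as the unit.

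**2. Number of questionnaire scores.** 24 teams x 2 members = 48, or 24 per arm. The figure 48 is derived; the article does not print it.

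**3. Standard error.** Let σ² be the variance of one score and ρ the within-team correlation (ICC).

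- Variance of the difference in arm means, assuming independence: σ²(1/24 + 1/24) = σ²/12.
- A team mean has variance σ²(1 + ρ)/2. With 12 teams per arm, the actual variance of the difference is 2 x σ²(1 + ρ)/(2 x 12) = σ²(1 + ρ)/12.
- The design effect is therefore 1 + ρ, the true standard error is √(1 + ρ) times the assumed one, and the effective number of scores is 48/(1 + ρ).

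**4. Type I error.** Null simulations used 12 teams of two per arm and 20,000 or more runs per value. Where independent runs differ, the range is shown. The ICC is an assumption throughout, because the article gives none.

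| Assumed ICC | √(1 + ρ) | Effective n | t-test on 48 scores | t-test on 24 team means |
|---|---|---|---|---|
| -0.2 | 0.89 | 60.0 | 2.7–2.8% | 5% |
| 0 | 1.00 | 48.0 | 4.8–5.0% | 5% |
| 0.1 | 1.05 | 43.6 | 5.9–6.2% | 5% |
| 0.3 | 1.14 | 36.9 | 8.4–8.7% | 5% |
| 0.5 | 1.22 | 32.0 | 10.6–11.4% | 5% |

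Mann–Whitney on a simulated 9-point scale behaves similarly: 5.6%, 7.8% and 10.1% at ICC 0.1, 0.3 and 0.5.

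**5. Fisher's test for satisfaction.** At 24 against 24 the test is conservative, at 2.5–2.9% with no correlation. With the ICC defined on a latent continuous scale, it reaches 4.9–6.0% at ICC 0.5. With the ICC defined on the yes/no response itself, it reaches 7.0–7.8% at 0.5. The definition should be stated whenever a figure is quoted.

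**6. The open cut.** For independent scores, taking the smaller Fisher p-value over the two middle cuts (the middle level on either side) gives a type I error of about 3–5% over several assumed distributions.

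**The case against.** **The article never says that the scores will be tested as independent.** This is true. It follows from the named tests and the absence of any team-level step, and the unit of analysis for questionnaire items is often settled in an analysis plan, which is not shown here. But section 2.9 commits to specific tests for these two outcomes, and applied to the data described in section 2.5.6 those tests are not valid as they stand. The objection lowers the certainty about what will be done. It does not make the text right.

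**The ICC is unknown, even in sign.** This stands. One member leads, and in the experimental arm one places the device while the other compresses (sections 2.5.1 and 2.5.5), so mental effort might be weakly or negatively correlated. The individual-level test would then be close to nominal or conservative. Team means hold the 5% level in every case, so the remedy does not depend on the answer.

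**The satisfaction cut.** A reader might infer that the cut will be chosen from the plot to produce a difference. The article says only that the plot comes first. The analyst works with coded groups and allocation-revealing data are deleted (sections 2.8 and 2.9). Searching all four possible cuts would inflate the error, but two of these would isolate a single extreme level and fit the class labels poorly. Between the two plausible cuts the error stays at about 5% or below.

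**Splitting the scale at all.** A reader might also object that two classes discard information. That is so, but a declared split of a secondary item is largely a matter of preference. A power comparison on 24 independent people per arm would rest on the very assumption questioned here.

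**Conclusion.** The point holds for the unit of analysis. If the tests in section 2.9 are applied to individual scores, the cognitive load comparison has the wrong error rate: roughly 6–11% instead of 5% for assumed ICCs of 0.1 to 0.5, and below 5% if the correlation is negative. Satisfaction is less exposed because Fisher's test starts out conservative. It stays near or below 6% up to a latent-scale ICC of 0.5, and somewhat higher if the correlation is defined on the yes/no response.

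These sizes rest on assumed correlations, two members in every team and 12 teams per arm. The missing cut for satisfaction is a minor gap in specification, not evidence of a data-driven choice.

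Only two secondary outcomes are touched. The primary outcome has one value per team, and the 24-team calculation is unaffected.

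**What to change.** In section 2.9:

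1. State that satisfaction and cognitive load are analysed at the level of randomisation. Either average the two members' scores and compare the 24 team values by arm, or fit a mixed model to the individual scores with a random effect for team and a small-sample correction. In either case allow for service, since allocation is stratified by it. If the two-class form of satisfaction is kept, the team value is the share of its two members who are satisfied.
2. State now which of the five Likert levels count as satisfied, in particular where the middle level goes.

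The cost is two or three sentences. No data, participants or procedures change. If teammates agree, the p-values will be slightly less favourable than those from individual scores, because they then reflect the information actually available.

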### 2.6. Equipment

For each study session, the same human patient simulator and the dedicated multiparametric monitor/defibrillator (Laerdal SimMan 3G, Laerdal Medical, Stavanger, Norway) will be used. All other equipment required for the scenario will be made available in the usual services intervention bags (factice medications will be used, e.g., sterile water). Teams will be briefed about the location and characteristics of equipment prior to the commencement of the scenario, before randomization. An i-gel^®^ device size 4 (Intersurgical Ltd., Wokingham, UK) and a lubricant tube will be available in the intervention bag.

### 2.7. Outcomes

The primary outcome will be the chest compression fraction (CCF) during the first two minutes of CPR (starting from first compression).

Secondary outcomes will be: CCF of each following 2 min cycle (from minutes 2 to 4, 4 to 6, 6 to 8 and 8 to 10), overall CCF (entire 10 min scenario), chest compressions depth; proportions of compressions within the depth target (5 to 6 cm), below target value (<5 cm) and above target value (>6 cm); chest compressions rate; proportions of compressions within the appropriate rate target (100 to 120 compressions per minute (cpm)), below target value (<100 cpm) and above target value (>120 cpm); proportions of compressions with complete chest recoil (<5 mm deviation from the reference value); time to first shock; time to first effective ventilation (defined as >300 mL [47,48,49,50,51]); ventilations volume; proportions of ventilations above target value (>700 mL), below target (<300 mL) and within target (300–700 mL); number of delivered ventilations; user satisfaction, and providers’ self-assessed cognitive load.

### 2.8. Blinding and Bias Minimization

To minimize bias during the study session, allocation will be disclosed as late as possible. Teams will be allocated only after the manikin and defibrillator characteristics presentation, and after the simulated patient’s condition has been given. From the moment of the allocation, there will be no more contact between investigators and participants. Thus, during the pre-scenario sessions, the teams will not have been allocated to one of the study arms, so the investigator responsible for the device workshop session is blinded to allocation. The participants are therefore also blinded during the workshop as well as in the self-managed training session.

Due to study design, which includes the use of a specific medical device, we will not be able to blind the participants during the study scenario. However, they will be blinded to the outcomes. Assessment bias will be limited, as the outcomes will be collected by an automated Laerdal manikin. The data analyst will also be blinded as to group allocation. Participants will be asked to withhold information until the end of the data collection process.

### 2.9. Sample Size Calculation, Data Extraction and Statistical Analysis

The sample size is based on an estimate as there are few relevant data available to compute it for such a study. The mean time required to deliver two ventilations is estimated to be around 4 s; two ventilations should be provided 5 times during the first cycle, therefore amounting to a total of 20 s of no-flow. In addition, the initial rhythm analysis should take about 8 s. Pooled together, these no-flow times should amount to 28 s out of the first 120 s cycle, therefore representing 23% of no-flow. The CCF should therefore be around 77% in the control group. In the experimental group, taking into account the time for rhythm analysis and shock, estimated to be around 8 s (same time as control group), the corresponding no-flow time should be about 7%, with a CCF of 93%. Based on observational data from case reviews and pilot tests, the variability of the data is estimated with a standard deviation of 12.

Twenty-four teams will be required in order to have a 90% chance of detecting, at the 5% significance level, an increase in the primary outcome measure from 77 in the control group to 93 in the experimental group.

The data extraction process will take place as follows: the CPREvents.xml file will be obtained by unzipping the SSX file proposed by Laerdal after each simulation with the SimMan manikin and saved in a comma-separated values (CSV) file. Then, this file will be uploaded in an SQL table (by phpMyAdmin, https://www.phpmyadmin.net/, V. 5.0.4, accessed on 23 February 2021). The variables of interest will be automatically generated in an accurate, reliable and reproducible manner using a PHP script specifically designed for the study (Supplementary File S7), from which a new CSV file will be extracted and imported directly into the statistics software. To minimize copying or typing errors, all data collected on paper CRF will be entered in duplicate using EpiData [52]. The consistency of the answers will then be checked by merging the two files in a common variable where discrepancies are listed. After resolving the discrepancies, data will be exported in a Stata DTA file. These two Stata databases will then be concatenated. Missing data will be treated as such. No imputation technique will be used.

All data that could allow the data analyst to identify the group allocation will be deleted (e.g., number of insertion attempts). The groups will be renamed otherwise (groups “Teysachaux” and “Moléson”) and the curated database will be sent in Stata DTA file format to DT for formal analysis. All investigators will be able to access the curated and coded data set.

Distribution normality will be checked graphically for continuous variables, and the Shapiro–Wilk test will be used in case of doubt. If this assumption is checked, a Student’s t-test will be used to compare both groups; if not, the Mann–Whitney U test will be used. These variables will be described using mean (SD) or median (Q1; Q3) depending on their distribution. We will test proportions using Fisher’s exact test. They will be reported with their 95% confidence interval.

User satisfaction will be assessed graphically, then dichotomized into “Satisfied” versus “Not satisfied” before being tested using Fisher’s exact test. The cognitive load variable will be treated as continuous.

A two-sided p-value of 0.05 will be considered significant. All the statistical analyses will be performed using Stata V15.1 (StataCorp. 2017. Stata Statistical Software: Release 15. College Station, TX: StataCorp LLC).

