The hypothesis is that the experimental approach could improve CCF during out-of-hospital cardiac arrest (OHCA), with a reasonable time of about 60 s to first effective ventilation.

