The simulated patient will be apneic and pulse will be absent if checked. The first compression will be defined as T0. After placement of the pads, the defibrillator’s display will show ventricular fibrillation (VF). To increase simulation’s fidelity CPR waves will be automatically displayed when compressions are delivered. All subsequent rhythm analyses will show refractory VF, regardless of whether a shock is delivered. Participants will be able to obtain an intravenous access on first attempt. They should administer first 1 mg of epinephrine (at the earliest after the second shock), then a first-dose of amiodarone or lidocaine following local protocols (in accordance with the 2020 AHA adult cardiac arrest algorithm) [44]. The scenario will be stopped exactly 10 min after the first compression. There will be no further intervention or educational adjunct after the study period.

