## 4. Discussion

The main limitation of this study is that it will be performed on a manikin, and that there will therefore be no direct evidence regarding actual clinical outcomes. Nevertheless, it is reasonable to assume that, if the CCF can be improved on a manikin, the same should hold true in an actual OHCA situation. However, the main difference between simulated and actual OHCA could rely on device insertion rate. Thus, should increases in the CCF be proven in this study, a further step could be a trial conduct in the field.

Due to the type of intervention, the blinding of participants to their allocated group will not be possible. Participants will, however, remain unaware of the study outcomes. Moreover, an objective measure of the main outcomes will be used continuously during the intervention to allow reliable assessment. The voluntary recruitment strategy could bias the sample, via a self-selection phenomenon which would give an unrepresentative sample of participants (with only those who are the most confident, motivated and involved that will take part in the study).

The seal pressure appears to improve over time in a number of humans due to the thermoplastic properties of the gel cuff [27], which may form a more efficient seal around the larynx after warming to body temperature. In this study, we will not expect such a good sealing because the manikin will not reach the appropriate temperature. This could make the manikin more difficult to ventilate.

The scenario represents one of the various contexts of OHCA: for instance, no first responder or medical reinforcement will be present on scene, and therefore the cardiopulmonary resuscitation will be managed with only two healthcare providers. This could impact several aspects of the secondary outcomes, due to fatigue or specific organization, and therefore limit the generalization of the results.

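### As the rules are written, a team that never delivers an effective ventilation would most naturally be excluded from time to first effective ventilation, a secondary outcome, although its failure is an observed result

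*Protocol article*

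**What the plan says.** Section 2.7 lists among the secondary outcomes "time to first effective ventilation (defined as >300 mL" (the bracket goes on to citations). Section 2.5.4 sets time zero at the first compression and limits observation: "The scenario will be stopped exactly 10 min after the first compression". For missing values, Section 2.9 says "Missing data will be treated as such. No imputation technique will be used". For continuous variables the same section names a Student's t-test if the distribution looks normal and a Mann-Whitney U test if not. It gives no censoring rule, no worst rank and no category for an event that never happened.

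Two other places give this outcome weight. The hypothesis in Section 1.1 couples a better chest compression fraction (CCF) "with a reasonable time of about 60 s to first effective ventilation". The Discussion expects a less good i-gel seal on a manikin that does not warm up, and adds: "This could make the manikin more difficult to ventilate".

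**The concern.** The missing-data rule suits a value that was lost, such as a failed recording. It does not suit a team that was fully observed for 10 min and never gave a breath above 300 mL. Nothing about that team is unknown: it has the worst possible result on this outcome. If it is treated as missing, the comparison is conditional on success, and success is itself affected by the approach being tested.

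At stake is the second half of the hypothesis. Delayed ventilation is the obvious price of placing a device first and giving no mask ventilation beforehand. An estimate restricted to teams whose airway worked could agree with the 60 s expectation however many teams failed. Assigning 600 s at the analysis stage would not clearly be open to the analyst either, because it could be read as the imputation that the plan rules out.

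**Working it through.** **Inputs from the documents.** 24 teams allocated 1:1 (Sections 2.5.1 and 2.9), an observation limit of 600 s (2.5.4), and an expected time of about 60 s (1.1). The significance rule is "A two-sided p-value of 0.05 will be considered significant".

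**The plan's own figure.** Section 2.9 states: "Twenty-four teams will be required in order to have a 90% chance of detecting, at the 5% significance level". The CCF values behind it are 77 for control and 93 for experimental teams, a difference of 16, and the standard deviation is taken as 12. Per arm, n = 2 × (1.960 + 1.282)² × 12² / 16² = 11.8, rounded up to 12, so 24 in total. The figure reproduces. It concerns CCF only and enters here just to fix 12 teams per arm.

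**Assumed.** The documents give no rate at which teams fail to reach 300 mL, so a range is shown.

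**1. Could it happen at all?** The chance of at least one failing team among 12 is 1 − (1 − f)¹²:

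| Failure rate f per team (assumed) | Chance of at least one failure |
|---|---|
| 5% | 46% |
| 10% | 72% |
| 20% | 93% |
| 30% | 99% |

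**2. Effect on the reported mean.** Let successful teams average 60 s and count k failures at 600 s. The mean is [60 × (12 − k) + 600 × k] / 12.

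- k = 1: (660 + 600) / 12 = 105 s
- k = 2: (600 + 1200) / 12 = 150 s
- k = 3: (540 + 1800) / 12 = 195 s

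With failures dropped, the mean is 60 s in every case. The median is much less sensitive: with 3 of 12 at 600 s, the sixth and seventh ordered values are still successes, so it stays near 60 s.

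**3. Effect on the rank test, fixed number of failures.** Simulated with 12 teams per arm, equal lognormal times among successes in both arms (median 60 s, log-SD 0.3, both assumed), and failures in the experimental arm only:

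| Failures of 12 | Rejection, failures ranked last |
|---|---|
| 1 | about 4–5% |
| 2 | 7% |
| 3 | 12% |
| 4 | about 21% |

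With failures dropped, rejection is about 4–5%, that is, no signal.

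**4. Effect on the rank test, random failures.** With normal times (mean 60 s, SD 15 s, assumed) and failure rates of 10%, 20% and 30% in the experimental arm, rejection is about 4% when failures are dropped. It is 6%, 11% and 22% when they are ranked last. If there is also a true delay among successes (45 s against 60 s, assumed) and 20% fail, rejection is 56% when failures are dropped and 79% when they are ranked last.

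With one or two failures, then, the loss lies mainly in the reported estimate and in the uncounted failures. The test loses appreciably with three or more, or when failures come on top of a real delay.

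**The case against.** The strongest objection is that exclusion is inferred. No sentence says that a team without the event is coded as missing. The variables are produced by a script in Supplementary File S7, which is not shown and may assign 600 s or a flag; a full analysis plan might also settle it. That stands as a limit on certainty. It does not remove the point, because the article does more than stay silent: it states a blanket rule, forbids imputation and names two tests, and together these lead to exclusion.

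A reader might also infer more than the documents support:

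- **That airway failures disappear from the trial.** They do not. A team that succeeds late keeps its late time. The number of ventilations is an outcome for every team, and ventilation volumes and the proportions below, within and above target are also outcomes. The number of insertion attempts is collected too, although it is removed from the analyst's file to protect blinding.
- **That this is the trial's designated harm outcome.** The protocol does not call it that. It is one secondary outcome among many, the primary aim concerns CCF alone, and no test against 60 s is planned.
- **That failures must be commoner in the experimental arm.** The Discussion expects a poorer seal than in warmed patients. It makes no comparison with face-mask ventilation and does not predict a full 10 min without one effective breath.
- **That time to first shock has the same problem.** The rhythm is ventricular fibrillation throughout, so a team with no shock is unlikely, and that would not be an airway failure.

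**Conclusion.** The point holds for one secondary outcome, time to first effective ventilation. Under the stated rules the natural reading excludes a team with no effective ventilation in 10 min, which makes both the comparison and the 60 s expectation conditional on success. In the illustration the reported mean stays at 60 s where counting failures at 600 s gives 105 to 195 s for one to three failures of 12. The median hardly changes, and the rank test changes little until about three failures.

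These sizes rest on an assumed number of failures, on placing failures in the experimental arm only, and on assumed distributions for the successful teams; the documents supply none of these. If every team ventilates effectively, nothing changes. The primary outcome (CCF in the first two minutes), the sample size and the main conclusion are untouched. The weight is therefore moderate. A claim that the trial's central finding is biased would go beyond the text.

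**What to change.** Add to Section 2.9, before data are seen by arm, wording such as: *A team with no ventilation above 300 mL by 600 s after the first compression is an observed result and not missing data. The number of such teams is reported by arm. Time to first effective ventilation is analysed with these teams censored at 600 s (Kaplan-Meier and log-rank test), or by a rank test in which they are ranked last. The term missing is limited to recording failures.* One of the two analyses should be chosen in advance.

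The extraction script needs a flag that separates no event from not recorded. The flag is defined alike in both arms. The same convention can cover time to first shock for consistency, although no problem is expected there.

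The cost is a few sentences, one script flag and slightly more analysis work. The reported time may also turn out less favourable to the experimental approach.
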